**Patient recruitment**			
	Screening questionnaire	Percentage of patients who agreed to participate in the screening survey	>80%: feasibility given <80%, reasons solvable by modification: feasibility likely <80% and reasons not solvable by modification: feasibility not given
	Screening questionnaire	Percentage of patients in screening survey meeting all inclusion criteria	>10%: feasibility given <10%, but reasons solvable by modification: feasibility likely <10% and reasons not solvable by modification: feasibility not given
	Screening questionnaire	Percentage of practices that enrolled 7-9 patients	>80%: feasibility given <80%, reasons solvable by modification: feasibility likely <80% and reasons not solvable by modification: feasibility not given
**Outcome evaluation**			
	T0 and T1 questionnaires	Percentage of patients who completed T0 and T1 questionnaires	>80%: feasibility given <80%, reasons solvable by modification: feasibility likely 80% and reasons not solvable by modification: feasibility not given
	General practitioner report	Patient drop-out rate	<20%: feasibility given >20%, but reasons solvable by modification: feasibility likely >20% and reasons not solvable by modification: feasibility not given

A range of secondary outcomes will be determined to gather information on potential effects of the program. All secondary outcomes are participant-reported and will be collected before (T0) and after (T1) the intervention by paper-based questionnaires which participants will complete at home and send directly to the study center.

Outcome measures on patient level comprise the German versions of the following validated instruments: Pain Disability Index German version (PDI-G) [24] (key secondary outcome), Patient Activation Measure [25], Short Form 12 Health Survey scale for health related quality of life [26], De-Jong-Gierveld loneliness scale [27], Pain Self-Efficacy Questionnaire German version [28], Avoidance-Endurance Fast Screening instrument [29], Pain-Catastrophising Scale [30], selected items of the European Project on Patient Evaluation of General Practice Care (EUROPEP) questionnaire on evaluation of GP care [31,32], and pain intensity (numeric analogue scale). Further study-specific items will be used to assess the use of self-care such as physical activity (3 items), relaxation techniques (1 item) and use of topical applications (1 item) and patients will be asked to document their pain medication (over-the-counter and prescribed). Secondary outcomes on GP and MA level refer to quality indicators for ambulatory pain management developed in the RELIEF project. Data for the process evaluation will be collected at various points in time as detailed in Figure 1.

During patient recruitment, practice teams will be asked to send the deidentified patient screening questionnaires to the study center for evaluation purposes. The e-learning for GPs and MA will be hosted on the platform Moodle on the server of the aQua Institute, Göttingen. After completion of the e-learning GPs and MA will be asked to fill in a short digitally provided survey to evaluate the training regarding aspects such as subjective knowledge increase, appropriateness of required time, appropriateness of didactical methods, and usability of the platform. The survey will be conducted through the survey tool Lime Survey hosted at a server of the University Hospital Heidelberg. Survey data will be linked through a pseudonym to the following meta-data gathered by the e-learning platform (e-learning completed or not completed, time needed to complete the e-learning (minutes), and number of logins necessary to complete the e-learning).

Patients will complete a paper-based pseudonymized questionnaire focusing on use and perceived usefulness of the provided educational material and experiences with study appointment 1. Patients will complete the questionnaire after going through the content provided and within 4 weeks after study appointment 1. At the end of the intervention period, patients will be asked to fill in a second questionnaire focusing on their experiences with study appointment 2 and 3 as part of the T1 follow-up survey.

All participating GPs and medical assistants will be invited to report their experiences during the pilot in a telephone interview. All patients will be invited to an interview after completing study visit 3. Depending on the response rate, a purposive sample of patients will be drawn. Written informed consent to participate will be obtained using separate information documents and agreement forms. Key questions on the interview guides will refer to intervention feasibility with regards to specified feasibility indicators, usefulness of provided material and tools, perceived effectiveness of the case and care management program, and suggestions for modifications from the perspective of health care providers and patients. Interviews will be recorded and transcribed verbatim. Transcripts will be pseudonymized and stored on secure servers at the Department of Primary Care, University Hospital Heidelberg. All audio files will be deleted after completion of data analysis.

### Data Analysis

A plan for the primary analysis will be finalized before data bank closure. All analysis will be performed in R (version 4.2.0 or higher; R Foundation for Statistical Computing) or in SPSS (version 28.0.1.0; IBM Corp) in a validated environment. The final analysis will be done as soon as the database has been declared to be complete and accurate and has been locked. Descriptive statistics will be provided to summarize demographics and baseline characteristics. In general, continuous variables will be described using number of observations, mean, SD, median, Q1, Q3, minimum, maximum, 95% CIs and, if existing, number of missing values at T0, T1 and for T0-T1 if appropriate. For categorical variables, absolute and relative frequencies will be given with missing values being reported as a separate category at T0 and T1. A CONSORT (Consolidated Standards of Reporting Trials) flow diagram will be created to display the progress of all participants through the trial. This includes the number of patients assessed for eligibility and the number of patients excluded because they did not meet inclusion criteria, declined to participate, or any other reason.

### Primary Outcome Analysis

For each objective of the intervention components and study procedures, a descriptive analysis will be performed to assess feasibility. For each objective, 95% CIs will be given based on the Wilson Score interval for binary measures [33]. Reasons for not fulfilling an indicator will be categorized and evaluated descriptively.

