### Intervention

The RELIEF intervention consists of five key components: (1) medical pain assessment and monitoring using a module specifically developed for the RELIEF intervention to be applied within an established case management software (CareCockpit) [20], (2) 3 scheduled structured appointments with GPs and medical assistants (MA), (3) e-learning on chronic pain management for GPs and MA, (4) educational video- and paper-based material for patients, and (5) a toolbox with a collection of resources for pain management for patients and practice teams. GP and MA will receive financial compensation for their additional efforts related to participation in the study (€200 [approximately US $216] per GP, €400 [approximately US $432] per MA) and number of included patients (€80 [approximately US $86] per included patient). GPs can apply for a total of 8 continuing medical education points upon completing the e-learning modules.

It is expected that patients participating in the case management program will benefit from the intervention. It is hypothesized that improved medication management and intensified use of nonpharmacological treatment strategies will result in a reduction in pain-intensity and pain-related disabilities, improved patient activation, more self-care activity and less use of analgesics. Figure 2 describes the assumed effect mechanism of the developed intervention.

It is assumed that adherence to guideline recommendations for CNCP by practice teams (green boxes) will improve if the intervention components (yellow boxes) effectively reduce identified barriers or make use of identified enablers respectively (blue boxes). Improved adherence to guideline recommendations will result in improved health outcomes or health behavior, respectively (gray box). Primary and secondary outcomes (gray box) focus on the effects of improved guideline adherence while adherence as well as assumed linkages between interventions and barriers are assessed within the scope of a comprehensive process evaluation.

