### Recruitment

General practices will be recruited through known contacts such as the established practice network of about 800 practices that use a particular case management system for chronically ill patients (PraCMan) [21] and a network of teaching and research practices affiliated with the Department of Primary care and Health Services Research, University Hospital Heidelberg. The target is to include 6 practices. Based on previous experiences, it can be assumed that about 10% of the practices approached are interested in participating in research projects. Therefore, 60 practices in a predefined region will be randomly drawn and an invitation to participate in the pilot study will be sent to them by postal or electronic mail together with a declaration of interest form. Practices that declare interest in participation will receive written information about study aims and procedures. In case the recruitment target is not met, another random sample will be drawn.

To identify eligible patients and to gather information on the prevalence of the target group in primary care, a screening survey will be conducted (see Data Collection and Outcomes section below). Eligible for participation will be adult patients with CNCP for more than 3 months, with at least moderate pain-related disability (minimum 4 points on a scale from 0-10), permanent or on-demand use of analgesics and co-analgesics in the previous 4 weeks, and practice team assessed ability to participate actively in the pilot study (sufficient cognitive abilities and internet access). Patients with cancer pain or in palliative care will be excluded. Recruitment target for each practice is 7-9 patients. If more than 9 patients agree to participate in the piloting, the practice team will select 7-9 patients who are according to their assessment likely to benefit from the program. Specific reasons for their choices will be explored in the process evaluation.

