### Data Collection and Outcomes

For the screening survey, each participating practice will hand out a screening questionnaire to the first 150 adult patients entering the practice from a defined date on. The practice team will collect the questionnaires, check eligibility with a provided template and invite all patients meeting the inclusion criteria to participate in the pilot study by handing out the study information material. The practice team will add information regarding reasons for nonparticipation, known CNCP diagnosis, known use of analgesics, and prescription of analgesics during the last month on the screening questionnaires of all patients meeting the inclusion criteria (regardless of whether they agree to participate in the study or not) by checking the patient file. The practice team will deidentify all questionnaires (also of patients without chronic pain) by cutting the lines for name and birthdate and send them to the study center for evaluation purposes regarding prevalence of patients in a primary care setting who meet the inclusion criteria.

Data collection related to medical pain history (used by practice teams only, not by researchers) comprises the following steps: patients receive a weblink from their GP practice leading to a browser-based app called TeleVital and complete the assessment through the app on their own digital device. TeleVital is a proprietary development of the Department of Primary Care and Health Services Research, University Hospital Heidelberg, and facilitates structured data collection in studies which use the CareCockpit. Data generated in the TeleVital app data will be stored on a secure server located at the University Hospital Heidelberg, Germany until it is transferred to the CareCockpit software installed in the GP practice. Data import will be initiated manually by the practice team at the next patient contact. Thus, practice teams will receive the assessment data only when the patient is present in the practice. Practice teams will use the assessment data for the purpose of diagnostics and treatment. It contains information on pain history, pain characteristics, use of analgesics, use on nonpharmacological measures, treatment targets, and items from validated screening questionnaires such as the Pain Detect questionnaire on neuropathic pain [22] and on mental comorbidities such as posttraumatic stress disorder [23].

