### Secondary Outcomes Analysis

As one of the aims of the study is to estimate the effect size, the 95% CI (2-sided) of the PDI-G percent change from baseline to T1 (T0-T1), which is planned to be the primary outcome in a subsequent cluster randomized trial and therefore of major interest in this pilot study, will be given. Only questionnaires with at least 6 out of 7 answered items will be considered. Missing items will not be imputed. Questionnaires with less than 6 answered items will not be considered.

As a sensitivity analysis, missing values of the PDI-G will be replaced on item level using multiple imputation based on predictive mean matching using the variables age, sex, center, and pain intensity at baseline as potential predictors. Missing scores and differences can then be calculated using the imputed items. Furthermore, a best- and worst-case scenario will be looked at, where missing values will be imputed by the highest and lowest observed value for T0 and T1 in the best case scenario and vice versa in the worst case scenario (lowest and highest observed value for T0 and T1, respectively). As another sensitivity analysis, a mixed linear regression model for the dependent variable PDI-G score at T1 will be performed including age, sex, and PDI-G at T0 as fixed effects and center as random effect. Descriptive analysis at item level and for the total number of pain-related patients at T0 and T1 will be done. Descriptive analysis of the item and score level will be done for all remaining secondary outcomes. For differences in scores between baseline and follow-up, 95% CIs will be reported. Missing values for secondary outcomes will not be imputed.

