No sample size calculation was performed, as the main purpose of the pilot study is to investigate feasibility of the applied interventions and study procedures. Considering the exploratory nature of the pilot study, and based on experiences from previously conducted research, a total of 50 patients is considered sufficient to provide an initial estimate of the potential effect of the intervention measured by the PDI-G percent change from baseline to T1 (T0-T1), which is the key secondary endpoint. Assuming a SD of 13.7 and 15.4 score points [34] corresponding to a SD of 19.6% and 22% score points respectively, a sample size of 50 patients and a 2-sided 95% CI would yield the following: assumed SD 19.6: [x-5.6, x+5.6]; assumed SD 22: [x-6.3, x+6.3], where x is the point estimate of the PDI-G percent change from baseline to T1 (T0-T1).

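### The prescribed Wilson intervals ignore clustering by practice: a serious loss of coverage for the screening proportions, a modest one for the 50-patient indicators

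*Protocol article*

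**What the plan says.** For the primary (feasibility) objective, the Primary Outcome Analysis section fixes the interval: "For each objective, 95% CIs will be given based on the Wilson Score interval for binary measures [33". It mentions no adjustment for practice.

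The data are clustered by design. Under Recruitment, "The target is to include 6 practices" and "Recruitment target for each practice is 7-9 patients". Screening is organised the same way: "each participating practice will hand out a screening questionnaire to the first 150 adult patients entering the practice from a defined date on". Table 3 makes the share of screened patients who meet all criteria one of the feasibility indicators, with a 10% threshold, so the Wilson rule applies to it. Overall Aim of the Study names the prevalence of the target group as a secondary objective.

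For the key secondary outcome, the Secondary Outcomes Analysis section says it will report "the 95% CI (2-sided) of the PDI-G percent change from baseline to T1 (T0-T1" without naming a formula. The precision statement in the same section, built on "a total of 50 patients is considered sufficient to provide an initial estimate", gives ±5.6 and ±6.3. Practice appears in two places only, both PDI-G sensitivity analyses: as a predictor for multiple imputation, and as a random effect in a linear model for the T1 score.

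**The concern.** The Wilson interval is derived for independent binomial observations. Here practice staff hand out and check the screening forms, import the pain assessment, hold the three appointments and, if more than nine patients agree, choose who enters. Several indicators in Tables 2 and 3 measure exactly these activities, so outcomes within a practice are likely to be alike. An interval that counts each patient as a full independent unit then claims more information than six practices provide.

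What is at stake is reported precision. These intervals are the only numerical measure of uncertainty planned for the feasibility indicators and for prevalence, and the study exists to inform a cluster randomized trial. A prevalence interval that is too tight would mislead planning of how many practices and screened patients that trial needs.

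**Working it through.** **Inputs from the protocol.** Six practices; 50 patients, so 50/6 = 8.33 per practice on average; 150 questionnaires per practice, so at most 6 × 150 = 900; PDI-G SD 19.6 and 22 (percent of scale); two-sided 95%. **Assumed:** ICC 0.01 to 0.10, because the protocol gives none.

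**1. The plan's own PDI-G figures.** An independent-patient t interval has half-width t(0.975; 49) × SD/√50:
- SD 19.6: 2.0096 × 19.6/7.071 = 5.57
- SD 22: 2.0096 × 22/7.071 = 6.25

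These round to the stated 5.6 and 6.3. The normal quantile gives 5.43 and 6.10, which do not match. So the stated precision contains no practice effect.

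**2. Design effect.** DE = 1 + (m − 1) × ICC, and n_eff = n/DE.

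| | ICC 0.01 | ICC 0.02 | ICC 0.05 | ICC 0.10 |
|---|---|---|---|---|
| Enrolled, m = 8.33: DE | 1.07 | 1.15 | 1.37 | 1.73 |
| n_eff of 50 | 46.6 | 43.6 | 36.6 | 28.8 |
| Screened, m = 150: DE | 2.49 | 3.98 | 8.45 | 15.9 |
| n_eff of 900 | 361 | 226 | 107 | 57 |

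**3. Screening prevalence at 10%.** The Wilson limits are [p + z²/2n ± z√(p(1−p)/n + z²/4n²)] / (1 + z²/n). With n = 900, the centre is (0.1 + 0.00213)/1.00427 = 0.1017 and the half-width is 1.96 × √(0.0001 + 0.0000012)/1.00427 = 0.0196, so the interval is 8.2-12.1%. With n replaced by n_eff:
- ICC 0.01: 7.3-13.5%
- ICC 0.02: 6.7-14.6%
- ICC 0.05: 5.6-17.2%

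In beta-binomial simulations with six practices of 150, the plain Wilson interval covers about 78%, 67% and 49-50% of the time at these ICCs, against 95% at ICC 0.

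Screening agreement, evaluated at 80% of 900, behaves the same way: 77.3-82.5% plain, 75.6-83.8% at ICC 0.01 and 71.4-86.5% at ICC 0.05.

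**4. The 50-patient indicators.** At an observed 80% the plain interval is 67.0-88.8%; it becomes 64.5-89.8% at ICC 0.05 and 62.3-90.6% at ICC 0.10. Simulated coverage of plain Wilson:

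| True proportion | ICC 0.01 | ICC 0.05 | ICC 0.10 |
|---|---|---|---|
| 80% | 94% | 91% | 86% |
| 90% | 96% | 94% | 91% |

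**5. PDI-G half-width with a practice effect.** Multiply the standard error by √DE. At ICC 0.05 (√1.367 = 1.17):
- 49 df: 5.57 × 1.17 = 6.5 and 6.25 × 1.17 = 7.3
- 5 df (t = 2.571): 8.3 and 9.3

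**The case against.** The strongest reply is that this is an exploratory, descriptive pilot in which no decision uses an interval. That is correct on the facts. Tables 2 and 3 rate point estimates against 80%, 10% or 20%, then ask whether the reasons are solvable, and two researchers settle the final assessment by consensus. A reader might infer that clustering could turn a feasibility rating; the documents do not support that. What remains is that an interval labelled 95% should cover about that often, and the screening interval may cover far less.

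A reader might also infer that every planned interval is wrong. That goes too far. One Table 3 indicator counts practices, so its unit is already the practice. The e-learning indicator is rated by GPs and medical assistants rather than patients. Whether patients find the educational material comprehensible may vary little between practices. At ICC 0.01 the 50-patient intervals widen by only about 4%.

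Nor does the protocol fix an independent-patient formula for the main PDI-G interval. That is inferred from the precision statement, and the analysis plan, to be finalized before database closure, is not shown. Practice is not ignored throughout either: the sensitivity model has a random centre effect. But that model addresses the T1 score, not percent change, and no feasibility proportion.

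Finally, a cluster adjustment is not automatically better. Near a true proportion of 90% with 50 patients, practice means with t on 5 df cover about 93% and 91% at ICC 0.05 and 0.10, against 94% and 91% for plain Wilson, and their upper limit often exceeds 100%. This stands and shapes the remedy.

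**Conclusion.** The point holds for the patient-level binary indicators, where the protocol names the method. It matters most for the screening proportions: because each practice contributes 150 patients, even an ICC of 0.01 makes the prevalence interval about 1.6 times as wide (6.2 against 3.9 percentage points). For the 50-patient indicators the loss is modest, and for some of them perhaps negligible. For PDI-G, what is established is that ±5.6 and ±6.3 assume no practice effect; the formula of the main interval is not stated.

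All sizes rest on assumed ICCs, equal or nearly equal practice sizes, and a beta-binomial model. The screening figures also assume that all 900 questionnaires are returned; with fewer, both the plain and the adjusted intervals are wider. The conclusion that the intervals are too narrow needs a positive ICC, which is likely given how the practices run the study but is not documented.

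**What to change.** - **Screening proportions (agreement, eligibility/prevalence):** replace plain Wilson with practice-level summaries and a t quantile on 5 df, or with Wilson on the effective sample size using a t quantile on 5 df. In simulation the practice-level summaries bring coverage back to 92-94%. Show the six practice-specific proportions.
- **50-patient indicators:** show the practice-specific proportions and report Wilson on n/[1 + (m − 1) × ICC] with the estimated ICC. Do not use practice means with t here, since they do no better near 90%.
- **PDI-G:** beside the main interval, report the percent-change interval from a model with a random practice effect. State that ±5.6 and ±6.3 assume no practice effect, and give the ICC 0.05 values from the working as an illustration.
- **Share of practices enrolling 7-9 patients:** keep plain Wilson.

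The cost is analysis wording and code, and the protocol leaves time for it because the analysis plan is closed only before database closure. The drawbacks are wider reported intervals and an imprecise ICC: with six practices and 50 patients near 90%, the estimate is zero or negative in roughly a third or more of simulated studies. The estimated ICC should therefore be reported as uncertain when it is carried to the cluster trial.
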